## Abstract

**Background:**

Many effective physical activity (PA) interventions have focused on individual factors or a single theoretical model, limiting our understanding of the determinants of PA practice and their interactions in the cancer trajectory. The present mixed-method study aims to capture social and psychological determinants of PA practice from diagnosis to remission among cancer patients, and to identify key levers for PA practice.

**Methods/design:**

A nested sequential mixed-method design QUAN (QUAL+QUAL) will be used, with qualitative studies embedded in the quantitative study to broaden our understanding of the determinants of PA practice. The design is sequential, since qualitative data on medical staff will be collected before patient inclusion (Phase 1), followed by quantitative patient data collection lasting one year (Phase 2) and a final qualitative data collection one year after inclusion (Phase 3). Phase 1 will be a case study in the two hospitals involved in the study, exploring knowledge of and support for PA practice among medical staff. Through interviews and documental analyses, the PA support dynamic will be evaluated with regard to PA prescription. Phase 2 will be a one-year observational study among 693 cancer patients. Quantitative medical, social, dispositional and psychological data, PA practices and preferences, will be collected at diagnosis, and six months and one year thereafter. Phase 3 will be a retrospective study, evaluating societal and policy factors, as well as unexpected factors playing a role in PA levels and preferences among cancer patients. For this phase thirty patients will be identified six months after inclusion on the basis of their PA profiles. Quantitative data will provide the main dataset, whilst qualitative data will complete the picture, enabling determinants of PA practice and their interactions to be captured throughout the cancer trajectory.

**Discussion:**

The present study aims to identify key levers and typical trajectories for PA practice among cancer patients, adapted to different times in the course of cancer and taking into account “what works”, “for whom”, “where” and “how”. The challenge is the tailoring of PA interventions to patients at different times in their cancer trajectory, and the implication of medical staff support.

**Trial registration:**

Clinical Trial NCT03919149, 18 April 2019. Prospectively registered.

## Background

In France, the number of patients living with cancer has increased in the last decade, due to higher remission rates, as well as larger number of diagnosed cancers [1, 2]. The literature has demonstrated that physical activity (PA) can play an important role in decreasing patient mortality rates and in increasing patient well-being at different times during their cancer [3, 4]. In other words, PA is beneficial in primary, secondary and tertiary cancer prevention [5], and helps decrease the side effects of treatment [6]. Previous work has shown that cancer patients tend to decrease their PA from diagnosis to the initiation of treatment [7] and have difficulty in recovering their initial PA level after treatment [8]. Nevertheless, studies focusing only on a specific time in the cancer trajectory (before, during or after) [9] or using a single theoretical model [10] have limited our understanding of the determinants of PA practice and its interactions, as well as of PA trajectories before, during and after cancer.

Different individual factors have been identified as playing an important role in PA practice. For example, gender, age, education level, socio-professional category, ethnicity, or overweight seem to impact PA levels in the general population [11] and among cancer patients [12]. Variables relating to personal disposition (traits), such as hope or optimism, have positive consequences on cancer [13–15], as they encourage the use of coping strategies, especially with regard to motivation [16], passion [17], and emotional regulation [18]. Moreover, physical activity prescription and social support from medical and paramedical staff seem to impact PA practice [19, 20]. While these variables appear to have an effect on PA practice, they are specific to individuals and to their direct environment, and their interactions have not often been analyzed [21].

Beyond the effect of the disease and its treatment, the socio-ecological approach has identified five groups of factors associated with PA practice: individual factors, interpersonal factors, environmental factors, policy factors and global factors [11]. While the first three concern individuals directly or their direct environment or context [22], the last two are more related to societal and policy determinants [23]. To our knowledge, research has mostly focused on one group of factors, especially the individual level, and very few studies have tried to capture all the different levels [21]. In addition, studies have mostly focused on testing the effectiveness of one theory, without crossing different theoretical models, and without taking both social and dispositional variables into account [24]. To be able to capture both the diversity and the interactions over time across the different factors [25], mixed methods are the most suitable. Indeed, by definition, a mixed method seeks to integrate both quantitative and qualitative data to gain a better understanding of a research problem [26], as each separate dataset is not sufficient to capture the trends and details of a situation [27].

### Study aims

The aim of this mixed-method study is to identify the variables of the socio-ecological model facilitating PA practice, as well as PA levels and preferences (see Fig. 1) at different times during the course of cancer (at diagnosis, during treatment, after treatment). The results from the present work will help to identify key levers of PA practice and their interactions among cancer patients, from diagnosis to remission, in a socio-ecological approach.

**Fig. 1 Fig1:**
[figure not shown]
Socio-ecological model used in present protocol

The specific objectives are:to evaluate the evolution of PA practices (level, context, preferences) from diagnosis to remission;to understand the interactions and reciprocal effects between sociological, dispositional, psychological and situational variables and PA level, and their evolution from diagnosis to remission;to analyze how policies and the social environment (medical staff) promote PA practice among cancer patient, crossing individual and interpersonal variables.

## Methods/design

The present study is designed as a mixed-method study using a sequential nested design QUAN (QUAL+QUAL) [28, 29]. The sequential design is based on a three-phase data collection process (see Table 1 for details), where qualitative data on medical staff will be collected before patient inclusion, followed by patient quantitative data collection lasting one year and a final qualitative data collection on a sample of patients one year after inclusion. The design will be nested because the three data collections will address different research questions, since the analysis of individual and interpersonal factors will be based on quantitative data and qualitative findings from medical staff, and patient data will complete the socio-ecological model for the social and policy environment. An interview guide will be used in the patient qualitative data collection, and the theoretical patient sampling for phase 3 will be informed by quantitative data from phase 2. The integration of the results will consist in the interpretation and explanation of the quantitative results, also making use of the qualitative results.

**Table 1 Tab1:** Description of the mixed method design

	Research question	Procedure	Data collection	Data analysis	Expected results	Data integration
Phase 1	What is observed among medical staff in terms of knowledge of and support for PA practice?	Case analysis per hospital	Interviews with health professionals using snowball sampling and document analysis	Content analysis using Nvivo software	Information on PA knowledge and support from medical staff, application of prescription requirements and orientation of patients to PA practice	Complete quantitative data on social support, public policies and organizational factors that encourage PA practice
Phase 2	What are the psychological and social factors influencing PA practice from cancer diagnosis to remission?	Cohort study on 680 patients included at diagnosis (T0; + 6 months; + 1 year)	Self-reported questionnaire	Descriptive, multivariate, multilevel analysis using SPSS, SAS and AMOS	Patient profiles for PA practice, theoretical model of interaction over time between social and psychological variables supporting PA practice	Quantitative data underpins the main data analysis Identification of patient profiles for the phase 3 study
Phase 3	What is the evolution of PA practice, PA preferences and what are the main barriers / facilitators from the time of diagnosis?	Qualitative study	30 patients with specific profiles identified in phase 2	Content analysis using Nvivo software	A list of factors, organized in the socio-ecological model to calibrate interventions	Broadening of the quantitative data and more detailed analysis of interactions with interpersonal and political variables

### Study setting

The present study will take place in the oncology departments of two hospitals in the north-east of France: the Lorraine Cancer Institute (ICL) and the Regional Hospital Center of Metz-Thionville.

### Ethics approval

Verbal informed consent will be obtained from each participant and they will be allowed to withdraw at any time without any consequences. Data will be made anonymous and only the first letter of the first name and surname and a number attributed to each patient will be recorded. This research complies with the Helsinki declaration and is registered with the French National Commission for individual privacy (CNIL) and to the French committee for individual protection (CPP). This research is registered on clinicaltrials.gov (NCT03919149).

### Phase 1: study involving medical staff

This phase is designed as a case-analysis [30], to explore knowledge and support on the part of medical staff (oncologists, nurses, physiotherapists, trainers in adapted physical activity) concerning PA practice among cancer patients.

#### Sampling method

As the study involves two different hospitals, the medical staff will be invited to participate in semi-structured interviews and to identify colleagues that would be willing to answer our questions, thus enabling a snowball sampling procedure [31].

#### Data collection

Semi structured interviews [32] with medical staff will be conducted, using an interview guide, based on the six dimensions of the Guide to good prescribing [33], adapted to physical activity.

#### Data analysis

The interviews will be fully transcribed and the content will be analyzed using both deductive methods (based on the Guide to good prescribing [33]) and inductive methods, where the interview content will be coded in the different dimensions of the model. Data will be interpreted by crossing responses obtained from the medical staff, to see which dimension of the Guide to good prescribing [33] can be applied, and to determine cancer patient trajectories. In addition, between and during the interviews, the means deployed to prescribe or support PA will be collected and analyzed, to enrich the data for each case.

### Phase 2: observational study

This phase is an observational study to explore the psychological and social determinants of PA practice among cancer patients from diagnosis to remission. Diagnosis is a moment when patients are particularly sensitive towards behavioral changes, if they are given the appropriate tools [34, 35]. The source population will include breast, colorectal and prostate cancer patients from two hospitals in north-eastern of France, to restrict heterogeneity of the cancers considered (see Fig. 2 for flow diagram).

**Fig. 2 Fig2:**
[figure not shown]
Flow diagram

#### Sample size and sampling method

The principal judgment criterion is the compliance with PA recommendations (i.e. 150 min of at least moderate PA per week). In a previous cohort study [36], 15% of breast cancer patients (*n* = 466) managed to comply with these recommendations. Considering the fact that patients with factors facilitating PA practice are twice as likely to comply with these recommendations (Odds Ratio = 2), with an alpha risk of 5% and a power of 80%, 660 cancer patients will be included (220 per cancer localization). Taking into account a potential loss of 5% of the patients (11 patients per localization), we hope to include and follow a total of 693 patients (231 for each cancer localization). The data collection will last 12 months, reaching 30 patient inclusions per month in each hospital.

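### The stated inputs (15% compliance, OR = 2, alpha 5%, power 80%) do not by themselves give 660 patients or 220 per cancer localization; read per localization, the power is about 53%

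*Protocol article*

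**What the plan says.** The protocol article, under Phase 2, Sample size and sampling method, names a binary main criterion: "The principal judgment criterion is the compliance with PA recommendations (i.e. 150 min of at least moderate PA per week"). The reference rate comes from an earlier cohort in which "15% of breast cancer patients" complied. The effect to be detected is that "patients with factors facilitating PA practice are twice as likely to comply with these recommendations (Odds Ratio = 2"). From these the text concludes that "with an alpha risk of 5% and a power of 80%, 660 cancer patients will be included (220 per cancer localization"). The loss allowance is built in the same unit: "Taking into account a potential loss of 5% of the patients (11 patients per localization"), leading to 231 per localization and 693 in total.

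The paragraph does not state what share of patients has the facilitating factor, whether the test is one- or two-sided, whether 15% is the rate without the factor or the overall rate, or whether the 80% belongs to each localization or to the whole cohort. Under Phase 2, Data analysis, PA levels are to be compared by hospital site and localization, followed by a latent class growth analysis and multilevel structural equation modeling. No test of determinants separately within each localization is announced there.

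**The concern.** The odds ratio compares patients with and without a facilitating factor. The sizes are given per cancer localization, which is a different grouping. A reader who sees 220 per localization next to 80% power, with the loss also added per localization, will naturally suppose that each cancer type is adequately sized. If it is not, a null result for a determinant in breast, prostate or colorectal patients alone would be taken as reasonably firm when it was close to a coin toss. For the pooled cohort, the power depends on how common the factor is, so one figure of 80% cannot hold for all the determinants the study examines.

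**Working it through.** **Inputs from the sample size paragraph:** reference compliance 15%; OR = 2; alpha 5%; power 80%; 660 in total, 220 per localization.

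**Assumptions where the paragraph is silent:** two-sided test; 15% is the rate without the factor; exposure split 50:50 first, then varied from 5% to 95%.

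**Step 1: rate with the factor.** Odds at 15% = 0.15/0.85 = 0.1765. Doubled = 0.3529. Rate = 0.3529/1.3529 = 0.2609, a difference of 0.1109. Mean rate = (0.15 + 0.2609)/2 = 0.2054.

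**Step 2: trying to reproduce the plan's figure.**

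n per group = [1.960·√(2·0.2054·0.7946) + 0.842·√(0.15·0.85 + 0.2609·0.7391)]² / 0.1109² = (1.1199 + 0.4763)² / 0.01229 = 207.3

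With continuity correction: (207.3/4)·[1 + √(1 + 4/(207.3·0.1109))]² = 225.0

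Other formulas give 205 (unpooled variance or arcsine) and 213 (log odds ratio) per group. An even split therefore needs about 416 to 450 patients in total by the two main formulas. A logistic-regression formula with an even binary factor gives 339 to 513 in total, depending on the event rate used. None of these gives 220 as a whole localization, or 660 as a total at an even split.

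**Step 3: power if the 80% is per localization (110 v 110).**

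- Standard error under the null = √(0.2054·0.7946·2/110) = 0.05448; under the alternative = √((0.1275 + 0.1928)/110) = 0.05396.
- z = (0.1109 − 1.960·0.05448)/0.05396 = 0.076, so power = 53.0% (simulation 53.2%).
- Maximum over all exposure splits: 53.4%, at about 45% exposed.
- All 231 patients retained: 55% at 50:50. One-sided test: at most 65%.
- OR detectable with 80% power: about 2.5 at 50:50, 2.7 at 30% exposed and 3.0 at 20% exposed.

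**Step 4: power if the 80% is pooled (n = 660).**

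| Share with the factor | Power for OR = 2 |
|---|---|
| 10% | 62% |
| 15% | 75% |
| 18% | 80% |
| 20% | 83% |
| 30% | 91% |
| 50% | 94% |
| 79% | 81% |
| 80% | 79% |

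Power is 80% or more between shares of about 18% and 79%. The OR detectable at 50:50 is 1.75.

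**Step 5: the two effect definitions.** A doubled probability is 15% to 30% and needs about 121 per group. OR = 2 is 15% to 26.1% and needs about 208 per group (207.3 rounded up). The ratio is 208/121 = 1.72, so the choice matters for the size.

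**Sensitivity.** If 15% is the overall rate, power at 50:50 falls to about 43% per localization and 88% pooled.

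**The case against.** The strongest defence is that the sentence attaches the 80% to 660 patients and that the figure in parentheses is only an allocation. On that reading the cohort does deliver 80% or more over a wide range of prevalences, and at 20% prevalence with continuity correction the power is 79.6%, practically the stated figure. Allowance for other covariates could also raise 416 to 450 towards 660. A condensed article may leave such details to the full protocol. The three cancers are presented as one source population, and the Data analysis section plans no determinant test within each of them.

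Much of this stands, and it rules out three stronger readings that a reader might infer:

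- *That the 80% is wrong however it is read.* It is not: the pooled cohort reaches it for factors present in about 18% to 79% of patients.
- *That a size for one exposure group was mistakenly reused as a localization total.* The figure of 220 does lie between 207 and 225, but the text does not say how it was obtained. A risk ratio of 2 tested one-sided with continuity correction gives 216 in total, which is also close, although it sets aside the stated odds ratio and assumes a one-sided test that is nowhere mentioned.
- *That a planned analysis is underpowered.* No within-localization determinant test is stated, so 53% describes an analysis that the wording invites, not one that is announced.

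What does not stand is the view that nothing needs changing. The size and the loss allowance are both built localization by localization, and at that level no exposure split brings 220 patients near 80% for OR = 2. Nor is the mismatch between doubled probability and odds ratio purely editorial. The parenthesis suggests which one was used, but the two imply sizes about 70% apart, and under the doubled probability 220 patients would give 76% two-sided instead of 53%.

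**Conclusion.** The concern holds in limited form. The stated inputs do not determine the stated sizes. Per localization, 220 patients have about 53% power for OR = 2, with a ceiling of 53.4% over all splits. Pooled, 660 patients have 94% at an even split and at least 80% for factors present in about 18% to 79% of patients, but only about 62% for a factor present in 10%. These figures rest on a two-sided 5% test, 15% as the rate without the factor, and an unadjusted comparison of two proportions. The pooled cohort is adequate for common factors, so the design is not in question. The statement of what it is powered for should be corrected, but it is not a fault that must stop the study.

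**What to change.** Rewrite the sample size paragraph, leaving recruitment at 660 before loss and 693 with the allowance:

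1. State that the 80% applies to the pooled cohort, with a two-sided 5% test, taking 15% as the rate without the factor.
2. Define the effect as 15.0% versus 26.1% (OR = 2) and drop the phrase that describes it as a doubled likelihood.
3. State that 660 patients give at least 80% power for factors present in about 18% to 79% of patients, with 94% at 50% and about 62% at 10% as reference points.
4. State that any analysis of determinants within one localization has about 53% power at best for OR = 2 (detectable OR about 2.5 at an even split) and is exploratory.

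The cost is wording only, with no extra patients and no change to the analysis. The downside is that the stated power becomes less favourable for localization-specific results and for rare factors. If the sponsor does want 80% within each localization, about 416 to 450 patients in each would be needed at an even split, or 1,248 to 1,350 over the three before loss. That would be a different study.

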#### Eligibility criteria

The inclusion criteria are:Being aged 18 years and older,Newly diagnosed with breast, prostate or colorectal cancerHaving been referred to an oncologist before the beginning of any treatment for cancerBeing able to provide informed consent to participate in the study

The exclusion criteria are:Presence of a threatening bone lesionPhysical, cognitive or linguistic inability to fill in the questionnaireEstimated patient life expectancy under 6 months (oncologist’s clinical opinion)Under custodial sentence or legal protection

Exclusion criteria in the course of the study are:Breast, colorectal or prostate tumor shown to be non-cancerous following anatomo-pathologic examinationProstate cancer patients that are only on active surveillance

#### Scales

The questionnaire will include four main sections and different scales: medical and socio-economic variables, personality traits, situational variables and physical activity. The scales will be chosen on the basis of their validation in French and their suitability to PA and cancer patients, when available.

Medical data will be completed by the clinical research assistant, and will include: patient care plan, actual patient trajectory (treatment completion, frequency, type), symptoms and complementary treatment (fatigue, pain, nutrition).

Sociological variables will include age, gender, education, socio-professional category, professional activity, marital and socio-economic status, and place of residence. An 11-item scale to evaluate precariousness and health inequality (EPICES scores, [37]) will explore all the dimensions of precariousness. Life habits (tobacco, alcohol, substance use) and PA practice before diagnosis will help to identify inter-determinant relationships. Medical data (co-morbidities, fatigue, sleep, pain) will also be collected from patients’ perspective.

Personality traits will be approached via two validated scales: Trait Hope [38] and Trait Optimism [39]. Trait Hope will be assessed using the Dispositional Hope Scale [40], validated in French [38]. The Trait Hope Scale contains four “agency” items, four “pathway” items, and four “filler” items. Respondents will be asked to rate the items on an 8-point Likert scale ranging from 1 “definitely false” to 8 “definitely true”. The Life Orientation Test-Revised (LOT-R, [39]), comprises six items and four fillers, and will be rated on a 5-point Likert scale, ranging from 1 “strongly disagree” to 5 “strongly agree”.

Situational variables will include passion [41], satisfaction of basic needs in sport [42], state-hope [38], self-determined motivation for PA [43], anxiety and depression [44]. The two dimensions of passion (harmonious and obsessive) will be measured on a 12-item scale [41], where answers will be rated on a 7-point Likert, ranging from 1 “totally disagree” to 7 “totally agree”. The basic needs satisfaction (autonomy, competence and relatedness) will be collected using a validated French scale in the sports context [42]. Participants will answer on a 7-point Likert scale, ranging from 1 “totally wrong” to 7 “totally true”. The Adult dispositional Hope scale [38] will be used to explore state-hope. This scale includes 6 items (2 dimensions: operational and motivational components), and will be answered on a 6-point Likert scale, ranging from 1 “totally disagree” to 6 “totally agree”. All six dimensions of self-determined motivation for PA [43] will be explored using an 18-item scale, with a 6-point Likert response scale ranging from 1 “does not correspond at all” to 6 “corresponds totally”. The Health Anxiety Depression Scale, adapted into French [44] will measure anxiety (7 items) and depression (7 items), on a three-point scale.

Physical activity and sedentary behaviors will be measured using the self-reported Global Physical Activity questionnaire [45]. This questionnaire will measure the frequency, intensity, and duration of PA practice, as well as its context (work, mobility or leisure). PA preferences will also be evaluated in terms of type of practice, duration, intensity etc. [46].

